**List of changes to the Statistical Analysis Plan**

Update on 10^th^ April 2024

1. The data were planned to be followed until the 31^st^ of January 2024 and be analysed in February and March. In practice, further follow-up was obtained till the 19^th^ of April, and the timing of analysis was till the 3^rd^ of May 2024.

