## Follow-up

Attendance assessed from date of invitation until the end of January 2024 (data extraction date).

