### Data linkage and variable derivation

The following variables are derived based on the source data.

| Variable | Definition | Notes |
| --- | --- | --- |
| *service* | Screening service | - Derived from service of which each data was extracted from: - 1, Central and East London (pilot area). - 2, Outer Northeast London. - 3, North London. - 4, Cambridge. - 5, North and East Devon. - 6, Doncaster. - 7, Dudley, Wolverhampton and Southwest Staffordshire, and - 8, East Lancashire. |
| *appointmenttag* | Tag each appointment, in the chronological order of appointment date. | Derived from *date*, labelled 1, 2, 3, etc by the chorological order of each appointment offered/ booked.  For reshaping data between wide and long format, each line represents either an appointment or per woman. |
| *flagadminerror* | Flag for administrative errors that wrong type of invitation letter was sent. | Derived from *flag2oiinviteandnotaoicl* and *flag3tabutanoiletterused.*   - 1, if Y on either variable above, error. - 0, otherwise, no error.   Should be a very small proportion of the sample. |
| *90dayattend* | Primary endpoint, 90-day attendance since first offered appointment | Derived from *attendedappointment and date*.   - 1, if Y on *attendedappointment* and the difference between variable screeningdate and variable *date* is less than or equal to 90 days. - 0, if N on *attendedappointment*, or attended but the difference between variable screeningdate and variable date is greater than 90 days: |
| *180_survtime* | Follow-up duration | - If Y on *attendedappointment, then t*he number of days between variable *screeningdate* and variable *date* if it is less than or equal to 180 days. - Otherwise, then *t*he number of days between variable *date* and the 31^st^ of January 2024 or the end of 180-day follow-up, whichever is the first.   As the time of event/censoring time in cox regression. |
| *180dayattend* | Secondary endpoint, 180-day attendance since first offered appointment | - 1, if Y on *attendedappointment* and the difference between variable *screeningdate* and variable *date* is less than or equal to 180 days, or to the 31^st^ of January 2024, whichever is the first. - 0, if N on *attendedappointment*, or attended but the difference between variable screeningdate and variable date is greater than 180 days.   This is the event variable for cox regression. |

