| Table 3 **Primary and secondary endpoints by study arms** | | | | | | | |
| --- | --- | --- | --- | --- | --- | --- | --- |
| Study arm | Total invited | 90-day attendance | 90-day attendance (%) | 95%CI | 180-day attendance | 180-day attendance (%)* | 95%CI |
| TT | XX | XX | XX.X% | XX.X%, XX.X% | XX | XX.X% | XX.X%, XX.X% |
| OT | XX | XX | XX.X% | XX.X%, XX.X% | XX | XX.X% | XX.X%, XX.X% |
| TO | XX | XX | XX.X% | XX.X%, XX.X% | XX | XX.X% | XX.X%, XX.X% |
| OO | XX | XX | XX.X% | XX.X%, XX.X% | XX | XX.X% | XX.X%, XX.X% |
| Total | XX | XX | XX.X% | XX.X%, XX.X% | XX | XX.X% | XX.X%, XX.X% |
|  | | | | | | | |

*For the 180-day attendance, estimate from the KM graph, add the surv_table for this graph if possible.

| Table 4 **Primary analysis of the endpoints** | | | | | | |
| --- | --- | --- | --- | --- | --- | --- |
|  | Study arm | 90-day attendance | | | 180-day attendance* | |
|  |  | IRR | 95% CI | p-value ^a^ | RR | 95% CI |
| 1 | TT vs OO | X.XX | X.XX, X.XX | X.XXX | X.XX | X.XX, X.XX |
| 2 | TT vs OT | X.XX | X.XX, X.XX | X.XXX | X.XX | X.XX, X.XX |
| 3 | TO vs OT | X.XX | X.XX, X.XX | X.XXX | X.XX | X.XX, X.XX |
| 4 | TT VS TO | X.XX | X.XX, X.XX | X.XXX | X.XX | X.XX, X.XX |
| 5 | OT vs OO | X.XX | X.XX, X.XX | X.XXX | X.XX | X.XX, X.XX |
| IRR: incidence-rate ratio, CI: confidence interval, RR: relative risk. a. Report p-value to 2sf.  *For the 180-day attendance, estimate from the KM graph. | | | | | | |

| Table 5 **Secondary analysis of the endpoints** | | | | | |
| --- | --- | --- | --- | --- | --- |
|  | 90-day attendance | | | 180-day attendance* | |
|  | IRR | 95% CI | p-value ^a^ | RR | 95% CI |
| (TT+TO) vs (OT+OO) | X.XX | X.XX, X.XX | X.XXX | X.XX | X.XX, X.XX |
| (TT+OT) vs (TO+OO) | X.XX | X.XX, X.XX | X.XXX | X.XX | X.XX, X.XX |
| IRR: incidence-rate ratio, CI: confidence interval, RR: relative risk. a. Report p-value to 2sf.  *For the 180-day attendance, estimate from the KM graph. | | | | | |

| Table 6 Primary and secondary endpoint by subgroups. | | | | | |  |  |  |
| --- | --- | --- | --- | --- | --- | --- | --- | --- |
| Subgroup | Study arm | Total invited | 90-day attendance | 90-day attendance (%) | 95%CI | 180-day attendance | 180-day attendance (%) | 95%CI |
| IMD quintile |  |  |  |  |  |  |  |  |
| 1 | TT | XX | XX | XX.X% | XX.X%, XX.X% | XX | XX.X% | XX.X%, XX.X% |
|  | OT | XX | XX | XX.X% | XX.X%, XX.X% | XX | XX.X% | XX.X%, XX.X% |
|  | TO | XX | XX | XX.X% | XX.X%, XX.X% | XX | XX.X% | XX.X%, XX.X% |

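### The 180-day time and event variables apply the 31 January 2024 cut-off differently, and a woman screened after that date but within 180 days has no event code

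*SAP*

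**What the plan says.** SAP section 3.2.2 (Data linkage and variable derivation) defines the two variables behind the 180-day analysis.

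- *180_survtime*, attenders: the days between "variable *screeningdate* and variable *date* if it is less than or equal to 180 days". No calendar date appears in this clause.
- *180_survtime*, everyone else: the days between the offered date "and the 31^st^ of January 2024 or the end of 180-day follow-up, whichever is the first".
- *180dayattend* = 1: attended, and the gap from offered date to screening "is less than or equal to 180 days, or to the 31^st^ of January 2024, whichever is the first".
- *180dayattend* = 0: did not attend, or "attended but the difference between variable screeningdate and variable date is greater than 180 days".

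The Follow-up section says: "Attendance assessed from date of invitation until the end of January 2024 (data extraction date". The List of changes to the Statistical Analysis Plan says: "In practice, further follow-up was obtained till the 19^th^ of April". The Secondary endpoint methods section censors non-attenders at the end of follow-up without naming a date. The footnotes to the templates for Tables 3, 4 and 5 show where the variables are used: "For the 180-day attendance, estimate from the KM graph".

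**The concern.** The two rows supply the time and the event indicator of a single survival analysis, so they need the same end of observation. They do not have it. After 31 January the attender's clock runs on, the non-attender's clock has stopped, and the event row has no category for the attender.

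Whoever writes the derivation must then invent a code. If late attenders are coded 0, they are censored at the moment they attend, which is informative censoring. If they are left missing, they leave the analysis because of their outcome. In either case the 180-day attendance read from the Kaplan-Meier curve no longer estimates what it is meant to.

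**Working it through.** The plan gives no figure for this point, so there is none to reproduce. The check has three parts.

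**1. Who is affected.** A late attendance within 180 days requires first offered date + 180 > 31 January 2024.

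- 31 January 2024 − 180 days = 4 August 2023, so only women first offered after 4 August 2023 are affected.
- 19 April 2024 − 31 January 2024 = 79 days of further follow-up.
- 19 April 2024 − 180 days = 22 October 2023. With a 19 April cut-off, only women first offered after 22 October would be censored before day 180.

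**2. A worked case.** Take a first offered date of 1 November 2023.

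- Woman A is screened on 15 February 2024. Her gap is 106 days, so *180_survtime* = 106. Code 1 fails because she was screened after 31 January. Code 0 fails because she attended and 106 is not above 180.
- Woman B never attends. Her time stops at 31 January, which is day 91, although follow-up to 19 April observed her unscreened for 91 + 79 = 170 days.

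**3. Size.** Kaplan-Meier simulation with 200,000 women per calendar. All of the following are assumptions that the document does not supply: true 180-day attendance of 70%, 85% of attenders coming in days 0–30 and the rest spread evenly over days 31–180, and first offered dates uniform over the calendar shown. Data are followed to 19 April with 31 January left in the rows. The comparator is a consistent 31 January cap for everyone, which isolates the inconsistency from the shorter follow-up.

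| First offers (2023) | Consistent 31 Jan cap | Late attenders coded 0 (difference) | Late attenders missing (difference) | Common 19 April cut-off |
|---|---|---|---|---|
| Jan–Jul | 70.1% | 70.1% (0.0) | 70.1% (0.0) | 70.1% |
| May–Oct | 69.9% | 69.8% (−0.1) | 70.8% (+0.9) | 69.9% |
| Jul–Oct | 70.1% | 69.9% (−0.2) | 71.4% (+1.3) | 70.0% |
| 5 Aug–Oct | 70.2% | 69.6% (−0.6) | 72.1% (+1.9) | 70.2% |
| Sep–Oct | 68.3% | 67.5% (−0.8) | 70.9% (+2.6) | 70.0% |
| Sep–Dec | 67.8% | 66.8% (−1.0) | 70.9% (+3.1) | 69.7% |
| 15 Oct only | 65.0% | 65.0% (0.0) | 68.5% (+3.5) | 70.1% |

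The last row can be checked by hand. By 31 January (day 108), 65.0% have been screened, and 5.1% are screened later but within the data. Dropping the latter gives 0.650 / (1 − 0.051) = 0.685. Coding them 0 changes nothing here, because they are censored after the last counted event.

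In the last three rows even a consistent 31 January cap falls below 70%, because no woman can then be observed to day 180. With data extracted on 31 January, the rows as written and a consistent cap agreed exactly in every calendar. The common 19 April cut-off recovered the simulated truth (69.8% to 70.2%) to within 0.1 point in every calendar.

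**The case against.** The strongest reply is that the rows were written for a 31 January extraction. No later screening date could then be in the data, a cap in the attender clause would be redundant, and the rows agree. That is correct for the plan as first intended. The reply continues that when follow-up was extended, the cut-off in the derivations presumably moved with it. Obtaining 79 more days and still censoring at 31 January would serve little purpose, and the methods section censors at the end of follow-up without a date. A difference between a change log and the text is not in itself an error.

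What stands is that nothing in the document says 31 January was kept when the April data were analysed, so the bias is conditional. But the log is used here only for which data were analysed, and the current derivation rows still carry 31 January. On those data they leave a class of women without a code, and that gap lies in the rows themselves. If the code was in fact updated, only the text needs correcting.

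A reader might also infer that attendance could be pushed to 100%. That would require late attenders to count as events after all non-attenders have been censored, and the *180dayattend* row limits events to 31 January. It would also require every first offer to fall after 4 August 2023, and the document gives no invitation dates.

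**Conclusion.** The point holds in a limited form. The two rows apply 31 January 2024 inconsistently, and a screening after that date but within 180 days of the first offered date has no event code. Applied as written to data followed to 19 April, and measured against a consistent 31 January cap, they put the 180-day attendance about 0 to 1 point low with late attenders coded 0, or about 1 to 3.5 points high with them missing. There is no effect if all first offers were by 4 August 2023. These sizes rest on the assumed attendance pattern and calendars. For scale, the sample size section works with a difference of 8 points.

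Two further inferences are not supported. One is that the relative risks between arms are distorted: they come from the same curves, but the simulations are of a single group, no relative risk was computed, and the document gives no attendance timing by arm. The other is that the primary result is affected: the 90-day endpoint is binary, carries no 31 January date and is analysed by Poisson regression.

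**What to change.** Replace 31 January 2024 in both rows with one data cut-off, the actual end of follow-up (19 April 2024), and apply it to every woman:

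- end = min(*date* + 180 days, cut-off), with *date* the first offered date;
- if screened on or before end: event = 1, time = *screeningdate* − *date*;
- otherwise: event = 0, time = end − *date*.

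Every woman then has exactly one code, and attenders and non-attenders share the same end of observation. The cost is a small change to the wording of two rows and to the derivation code, with no new data. If the code already works this way, only the text changes.

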**Supplementary Tables**

**Supplementary Table 1**: Breast screening uptake in 2021/22 and Index of Multiple Deprivation (IMD) quintile of selected services determined by the NHSBSP prior to the start of the study

| **Code** | **Service** | **Uptake^a^** | **IMD Quintile^b^** |
| --- | --- | --- | --- |
| FLO | Central and East London | 42% | 3 |
| EBA | North London | 54% | 2 |
| FBH | Outer NE London | 58% | 1 |
| MDU | Dudley, Wolverh. & SW Staffords. | 60% | 2 |
| DCB | Cambridge | 61% | 5 |
| CDO | Doncaster | 63% | 2 |
| LED | North and East Devon | 67% | 4 |
| ^a^ Year 2021/22 figure^3^  ^b^ 1 being the most deprived and 5 being the least deprived.. | | | |

**Supplementary Table 2**: Characteristics of women included in the services evaluation by NHSBSP service.

|  | Service name | | | | | | | | | | | | | |
| --- | --- | --- | --- | --- | --- | --- | --- | --- | --- | --- | --- | --- | --- | --- |
|  | Doncaster | | Cambridge | | North London | | Outer NE London | | Central and East London | | North and East Devon | | Dudley,Wolverh&  SW Staffords ^d^ | |
| Age (Mean, IQR) ^a^ | 60.0 | 54.0 – 65.0 | 54.4 | 50,0-59.0 | 59.4 | 55.0-64.0 | 58.8 | 54.0-64.0 | 58.5 | 54.0.63.0 | 59.1 | 55.0-65.0 | 58.4 | 52.0-64.0 |
|  |  |  |  |  |  |  |  |  |  |  |  |  |  |  |
| IMD (quintile) |  |  |  |  |  |  |  |  |  |  |  |  |  |  |
| 1: most deprived | 628.0 | (23.2%) | 83.0 | (3.6%) | 382.0 | (12.7%) | 1018.0 | (61.1%) | 514.0 | (22.1%) | 199.0 | (8.1%) | 1489.0 | (44.8%) |
| 2 | 422.0 | (15.6%) | 91.0 | (4.0%) | 780.0 | (25.9%) | 619.0 | (37.2%) | 1346.0 | (57.9%) | 306.0 | (12.4%) | 803.0 | (24.2%) |
| 3 | 564.0 | (20.8%) | 356.0 | (15.5%) | 743.0 | (24.7%) | 22.0 | (1.3%) | 304.0 | (13.1%) | 775.0 | (31.4%) | 525.0 | (15.8%) |
| 4 | 719.0 | (26.5%) | 679.0 | (29.5%) | 796.0 | (26.5%) | 2.0 | (0.1%) | 125.0 | (5.4%) | 616.0 | (25.0%) | 426.0 | (12.8%) |
| 5: least deprived | 359.0 | (13.2%) | 1051.0 | (45.7%) | 285.0 | (9.5%) | 0.0 | (0.0%) | 26.0 | (1.1%) | 542.0 | (22.0%) | 73.0 | (2.2%) |
| missing | 18.0 | (0.7%) | 41.0 | (1.8%) | 21.0 | (0.7%) | 4.0 | (0.2%) | 11.0 | (0.5%) | 30.0 | (1.2%) | 9.0 | (0.3%) |
|  |  |  |  |  |  |  |  |  |  |  |  |  |  |  |
| Prevalence and age |  |  |  |  |  |  |  |  |  |  |  |  |  |  |
| prevalent and <60 | 494.0 | (18.2%) | 1556.0 | (67.6%) | 762.0 | (25.3%) | 356.0 | (21.4%) | 805.0 | (34.6%) | 631.0 | (25.6%) | 1015.0 | (30.5%) |

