# Study details

## Objectives

The primary objectives are to evaluate:

1. the effect of different combinations of timed appointments and open invitations on attendance in the NHS Breast Screening Programme; and

2. the effect as above in subgroups defined by index of multiple deprivation (IMD), and area-level summaries of ethnic diversity.

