## Subgroups

Subgroups for reporting are below, further details are in [section 3.2.1](#source_data_variable) and [section 3.2.2](#derived_variables):

1. IMD (quintile):
   - 1: most deprived
   - 2
   - 3
   - 4
   - 5: least deprived
2. Ethnicity(area-level):

- White
- Non-white

1. Combination of prevalent/incidence screen and binary age categories:
   - Prevalent and under 60
   - Incident and under 60
   - Age 60 and over
2. Screening services:
   - Central and East London (pilot area where the study was first run)
   - Outer Northeast London
   - North London
   - Cambridge
   - North and East Devon
   - Doncaster
   - Dudley, Wolverhampton, and Southwest Staffordshire
   - East Lancashire
3. Rurality of the screening site:
   - Rural
   - Urban
4. Mobility of the screening clinic:
   - Static, e.g. hospital
   - Mobile, e.g. van

Our focus lies in the first two subgroups, IMD quintiles and the area-level ethnicity.

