## Sample Size Justification

We aimed for a sample size of 16,000 women for the following reasons.

Previous results comparing timed to open invitations suggest an absolute 8% increase in participation with timed appointments compared to open invitations. As noted above, there is an interest in subgroup analyses. For a comparison of two groups with participation rates of 65% and 73%, 524 persons per group would give 80% power to detect this difference as significant at 5% level with two-sided testing. To allow for estimation of the primary outcome in socioeconomic and ethnic subgroups, we planned to evaluate 16,000 women in total (4,000 per arm).

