| *imdquintile* | Index of Multiple Deprivation in quintiles | First, small area level index of multiple deprivation 2019 (*imddecile*) by linking *lsoacode (*2011) with IMD2019 data^2^, then derive from deciles to quintiles.   - 1 (least deprived) - 2 - 3 - 4 - 5(most deprived) |
| *ethnicity* | ethnicity (area level estimate) | Small area level ethnicity estimate derived by linking source data with the ethnicity data from Office for National Statistics site^3^ with *lsoacode* as identifier, for women from aged 50 and above, by linking LSOA with census data. Expect in 5 major categories:   - - 1, Asian or Asian British   - 2, Black or Black British   - 3, Mixed   - 4, Other ethnic groups   - 5, White |
| *ethnicity_white* |  | - - Derived from *ethnicity* as defined above.   - 1, white   - 0, non-white |
| *rurality* | Whether the screening site is rural or urban. | Derived by linking source data with the data from open geography portal, on ‘Rural Urban Classification (2011) of Lower Layer Super Output Areas in England and Wales”^4^, using *lsoacode* as identifier.   - - 0, rural   - 1, urban |
| *age_prev_status* |  | Derived from *ageatfoa* and *prevalentincidentstatus:*   - - 1, prevalent and under60,   - 2, incident and under60,   - 3, over60, and   If *prevalentincidentstatus* is missing, impute based on *ageatfoa.* |
| *firstarm* | Open invitation or timed appointment at the first invite. | Derived from *armname* |
| *secondarm* | Open invitation or timed appointment at the second invite. | Derived from *armname* |
| Note: when the *lsoacode* cannot be identified in the sourcedate during data linkage, resolve from checking the data file: LSOA (2011) to LSOA (2021) to Local Authority District (2022) lookup for England and Wales. ^5^ | | |

**NOTE:** The original source dataset should not be altered. Any modification to data extract MUST be saved to a separate file.

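### The derivation table codes IMD quintile in the opposite direction to the subgroup definition and to every table that labels the direction, and Table 6 prints no direction at all

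*SAP*

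**What the plan says.** Section 3.2.2 is the working instruction for building the variable. It links each woman's small-area code to the 2019 deprivation deciles, "then derive from deciles to quintiles", and gives the codes as "1 (least deprived) - 2 - 3 - 4 - 5(most deprived".

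The Subgroups section under Study details lists the same five levels from "1: most deprived" to "5: least deprived", and sends the reader to 3.2.2 for further detail. The Table 1 and Table 2 templates and the row labels of Supplementary Table 2 follow the Subgroups section. So does the footnote to Supplementary Table 1: "1 being the most deprived and 5 being the least deprived".

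The Table 6 template, which holds attendance by arm within subgroup, labels its IMD rows only 1, 2, 3, 4 and 5.

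On the weight given to this subgroup, the second primary objective is to evaluate "the effect as above in subgroups defined by index of multiple deprivation (IMD), and area-level summaries of ethnic diversity", and the Subgroups section adds: "Our focus lies in the first two subgroups, IMD quintiles and the area-level ethnicity".

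**The concern.** The two definitions cannot both stand, and the section that defines the subgroup refers the analyst to the section that reverses it. No step in the SAP turns the scale round, and the list of changes shown deals only with follow-up and analysis dates. Text extraction does not explain the conflict, because both ends of both scales are written out in words.

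The layout makes a slip hard to see. An analyst who fills Table 6 from imdquintile as derived puts the least deprived women in row 1. A reader who takes the key from the Subgroups section or Table 1 reads row 1 as the most deprived. Nothing in Table 6 would expose the difference.

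At stake is the direction of the deprivation finding, which belongs to a primary objective. The Primary analysis section also commits to naming the best-performing strategy within specific subgroups whatever the tests show. If the strategies do rank differently across the deprivation scale, a reversed key would attach that ranking to the wrong women.

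**Working it through.** **1. Directions side by side**

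| Place in the SAP | Code 1 | Code 5 |
|---|---|---|
| 3.2.2, imdquintile | least deprived | most deprived |
| Subgroups | most deprived | least deprived |
| Table 1 and Table 2 templates | most deprived | least deprived |
| Supplementary Table 1, footnote b | most deprived | least deprived |
| Supplementary Table 2, row labels | most deprived | least deprived |
| Table 6 template | no label | no label |

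Tables 3 to 5 do not show IMD. No table uses the 3.2.2 direction.

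**2. The plan's own percentages.** Supplementary Table 2 reproduces. Outer NE London: 1,018 / (1,018 + 619 + 22 + 2 + 0 + 4) = 1,018 / 1,665 = 61.1% in quintile 1. Cambridge: 1,051 / (83 + 91 + 356 + 679 + 1,051 + 41) = 1,051 / 2,301 = 45.7% in quintile 5.

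**3. Size of the worst case.** Sums over the seven services:

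- Quintile 1: 628 + 83 + 382 + 1,018 + 514 + 199 + 1,489 = 4,313
- Quintile 2: 422 + 91 + 780 + 619 + 1,346 + 306 + 803 = 4,367
- Quintile 3: 564 + 356 + 743 + 22 + 304 + 775 + 525 = 3,289
- Quintile 4: 719 + 679 + 796 + 2 + 125 + 616 + 426 = 3,363
- Quintile 5: 359 + 1,051 + 285 + 0 + 26 + 542 + 73 = 2,336
- Known IMD: 17,668. Missing: 134. Total: 17,802.

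Reading one scale with the other's key replaces quintile q by 6 − q. Only quintile 3 keeps its label. Mislabelled: 4,313 + 4,367 + 3,363 + 2,336 = 14,379, and 14,379 / 17,668 = 81.4%. The 4,313 most deprived women (24.4%) would change places with the 2,336 least deprived (13.2%), and the 4,367 in quintile 2 with the 3,363 in quintile 4.

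**4. Which direction do the filled data follow?** For each service, take the mean quintile from Supplementary Table 2, Σ(q × n) / Σn, and compare it with the service quintile in Supplementary Table 1, described there as determined by the NHSBSP before the study. Outer NE London, for example: (1,018 + 2 × 619 + 3 × 22 + 4 × 2) / 1,661 = 2,330 / 1,661 = 1.40.

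| Service | Suppl. Table 1 | Mean as printed | Mean if reversed (6 − mean) |
|---|---|---|---|
| Central and East London | 3 | 2.05 | 3.95 |
| North London | 2 | 2.94 | 3.06 |
| Outer NE London | 1 | 1.40 | 4.60 |
| Dudley, Wolverhampton and SW Staffordshire | 2 | 2.03 | 3.97 |
| Cambridge | 5 | 4.12 | 1.88 |
| Doncaster | 2 | 2.91 | 3.09 |
| North and East Devon | 4 | 3.41 | 2.59 |

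The mean absolute difference is 0.67 as printed and 1.88 if reversed. The Spearman correlation is +0.82 as printed and −0.82 if reversed. With seven services this is descriptive only, but the two supplementary tables clearly run in the same direction, with 1 = most deprived.

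**5. What does not depend on the coding.** IMD enters none of the models or ordered tests for the overall arm comparisons. The sample size of 524 per group for 65% against 73% reproduces (pooled variance, no continuity correction) and does not use IMD.

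**The case against.** The strongest reply is that this is a labelling slip that did no harm. The completed Supplementary Table 2 puts Outer NE London mostly in quintile 1 and Cambridge mostly in quintiles 4 and 5, which agrees with Supplementary Table 1. Estimates of attendance within each quintile are the same under either coding; only the row name changes. An analyst filling Table 1, which spells out the direction, would have a good chance of noticing the clash. The 81% is the result of a hypothetical swap, not an observed error.

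Much of this stands. A reader might infer that the IMD results were reported upside down. The documents do not support that: the only filled IMD table points to 1 = most deprived, and no filled Table 6 is shown. A reader might also infer that every results table contradicts 3.2.2. That goes too far as well, because the tables that label the direction describe women or services, and Table 6, the one outcome template with IMD, has no label.

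What the reply does not remove is the contradiction. Supplementary Table 2 is descriptive and does not show how the subgroup outcomes were coded. Anyone repeating the analysis from 3.2.2 would obtain the opposite scale.

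**Conclusion.** The point holds as an internal contradiction in an operative variable definition. Section 3.2.2 is wrong as written: it disagrees with the Subgroups section and with every table that states a direction, and the filled data side with those.

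The consequence is conditional. It arises if imdquintile is derived as 3.2.2 says and its values are then read against the other labels. In that worst case 14,379 of 17,668 women with known IMD (81%) carry the wrong quintile label. How far this would change the conclusion depends on whether the effect of invitation strategy varies with deprivation, which the document does not show.

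The overall arm comparisons and the sample size are unaffected. Because the subgroup belongs to a primary objective and the correction is trivial, it should be made.

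**What to change.** 1. In section 3.2.2, define imdquintile as 1 = most deprived through 5 = least deprived, to match the Subgroups section and the labelled tables.
2. State there which pair of deciles forms each quintile, and which end of the decile scale is the most deprived.
3. In Table 6, print the direction on rows 1 and 5.
4. Confirm that the code behind the IMD subgroup results uses this direction. A simple check is that Outer NE London should fall mostly in quintile 1 (61.1% in Supplementary Table 2). Apply it to the dataset that feeds Table 6, not only to the descriptive table.

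The cost is a few lines of SAP text, two row labels and one check of the code. There is no statistical trade-off.
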